## Abstract

**Background:**

Providing optimal care for critically ill patients is an extremely important but also highly demanding task, both emotionally and physically. The “ICU Support” team meeting concept aims to support intensive care unit (ICU) teams by promoting interprofessional communication, peer support, and patient safety by providing a structure for daily team meetings. This protocol describes a study to explore the effectiveness of “ICU Support” for patient- and staff-centered outcomes.

**Methods:**

ICU Support will be implemented at nine university hospitals located in Germany, following a two-arm randomized parallel group design with an intervention and a control condition and three data collection periods. In the intervention arm, leading ICU personnel (physicians and nurses) will be trained in ICU Support and implement the ICU Support elements into the daily work routine of their units upon completion of data collection period T0 (baseline). In the control arm, ICU Support will not be implemented until the completion of the data collection period T1 (1 month after study start). Until then, the regular daily schedule of the ICU teams will be maintained. The final data collection period (T2) will take place 4 months after the start of the study. Primary outcomes include the number of intensive care complications per patient during their ICU stay during T1 and the sick-related absence of ICU staff during T1. Secondary outcomes include, among others, the average severity of intensive care complications per patient and employee self-reported data regarding their teamwork and patient safety behaviors.

**Discussion:**

The need for healthy and well-trained ICU staff is omnipresent; thus, structured and evidence-based interventions aimed at supporting ICU teams and facilitating patient safety are required. This multicenter study aims to explore the effectiveness of ICU Support for patient- and staff-centered outcomes. The insights derived from this study have the potential to significantly improve ICU patient safety, staff communication, and connectedness and decrease sickness-related expenses and social costs associated with high work demands among ICU staff.

**Trial registration:**

German Clinical Trials Register DRKS00028642. Registered on 4 April 2022.

## Administrative information

**Table Taba:** 

Title {1}	Effects of the “ICU Support” team meeting concept on patient-centered and staff-centered outcomes: study protocol for a randomized controlled multicenter study
Trial registration {2a and 2b}	Registration in the German Clinical Trials Register since 4 April 2022 (DRKS00028642) https://www.drks.de/drks_web/navigate.do?navigationId=trial.HTML&TRIAL_ID=DRKS00028642
Protocol version {3}	22.10.2022, Version 1.0
Funding {4}	No external funding was or will be received for the design of the study, the collection, analysis, and interpretation of data as well as the writing of the manuscript

## Introduction

### Background and rationale {6a}

Intensive care unit (ICU) teams face the important challenge of providing optimal care for critically ill patients. This task is not only complex but also highly demanding, both emotionally and physically. Consequently, ICU professionals report increased levels of stress, exhaustion, and sick-related absence from work [1, 2]. This, in turn, can negatively affect the quality of patient care as, for example, reflected in an increased number of treatment errors and mortality [3, 4]. Medical errors can further elicit work-related stress in healthcare professionals [5]. Such a series of events may lead to a vicious circle that has been further exacerbated by the current COVID-19 pandemic [6]. The need for healthy and well-trained ICU teams has substantially grown ever since. Yet, there still exists a profound gap between the requirements placed on ICU teams to provide optimal patient care (e.g., adapting to fast-paced changes in the workflow, being emotionally resilient) and how work is typically structured and paced at ICUs. For example, improvements of work processes, interprofessional understanding, and psychological support require time and substantial coordinative efforts that are oftentimes missing during stressful shifts.

Previous research suggests that an important means to counteract the impairment of patient safety and demoralization of ICU professionals are *after-action reflections* (also known as *debriefings*) that promote interpersonal contact and collective learning from experiences [7]. If properly conducted, debriefings promote effective teamwork and improve patient care. In their meta-analysis, Tannenbaum and Cerasoli (2013) demonstrated that organizations can improve individual and team performance by 20–25% by applying debriefings. Their findings further suggest that this effectiveness can be boosted through effective facilitation and structure [8]. Additionally, previous research shows that specific debriefing tools not only provide teams with the opportunity to critically reflect on but also foster employees’ emotional health and well-being [7]. Building on this evidence, the meeting concept “ICU Support” was specifically designed for ICU teams to facilitate regular, supportive, and adaptive team interaction and reflection to promote employee well-being and patient care.

ICU Support is based on the “Circle Up” framework [9] which suggests a process for successfully integrating daily team meetings into clinical practice. Following this process, short meetings at the beginning and end of a shift (approx. 5 min each) are supplemented by situational check-ins during work to optimally support employees in a psychologically safe climate. Preliminary data suggests that Circle Up improves work processes and teamwork and promotes interprofessional peer connectedness and well-being [9]. ICU Support builds on guiding principles underlying effective teamwork in healthcare as proposed by Circle Up: [1] supporting the psychological well-being of employees (e.g., through peer support and the opportunity to contribute to solutions) [2] promoting psychological safety by creating an open, appreciative atmosphere in which employees feel safe to share their ideas or ask for help if needed [10] and [3] regularly facilitating the provision of high-quality feedback. Further, ICU Support combines these principles into the promotion of [4] *safety management*—a principle that seems particularly relevant in an ICU context, where treatment errors often lead to disastrous consequences for patients. Safety management refers to the regular team reflections in which critical incidents and treatment errors are collectively identified and analyzed, so that the number of adverse events is minimized [11]. Thus, next to fostering employee well-being through team cohesion and peer support, ICU Support aims to directly improve patient safety at ICUs by installing a system of reporting, discussing, and integrating team members’ insights to collectively learn from errors and to identify solutions.

### Objectives {7}

The aim of the research project presented here is to evaluate the effectiveness of ICU Support regarding (1) ICU patient outcomes and (2) ICU staff outcomes. More concretely, the *primary objective* of this study is to test the hypotheses that the ICU Support intervention (a) reduces the occurrence of complications in intensive care patients and (b) reduces sickness-related absence among intensive care unit staff. *Secondary study objectives* include investigating whether ICU Support improves the perception of ICU staff regarding team collaboration and interaction related to patient safety, as well as exploring how potential effects of the ICU Support intervention develop over time.

### Trial design {8}

The present study is designed as a superiority trial, employing a two-arm randomized parallel group approach and three data collection periods. This design enables the inclusion of both an intervention group and a control group, allowing for a robust comparison of outcomes for demonstrating potential superiority of the intervention compared to the control. Nine university hospitals in Germany will be participating in the study and will be randomly divided into two study arms:

#### Arm 1: intervention

Upon completion of data collection period T0 (baseline), ICU senior personnel (physicians and nurses) will be trained in the ICU Support concept. Simultaneously, other ICU team members will be informed about the content and background of the ICU Support concept by means of a short, standardized information video. With the start of the study, the managers introduce the ICU Support elements into the daily work routine of their units. In this arm, the intervention will be maintained throughout the course of the study and will be supervised and monitored by a staff member from outside the unit.

#### Arm 2: control

In this study arm, ICU Support will not be implemented until the completion of data collection period T1. Until then, the regular daily schedule of the ICU teams will be maintained. However, to avoid a possible confounding of results by a Hawthorne effect (change in performance due to the knowledge of participating in a study) [12], managers and staff in both study arms will be informed about the content and aim of the study after the end of the survey period T0. Upon completion of data collection period T1, ICU managers will be trained in the ICU Support concept, analogous to the intervention arm.

An overview of the study design is shown in Fig. 1.

**Fig. 1 Fig1:**
[figure not shown]
Study design

Compared to other study designs (e.g., cross-over design), the current study design allows to explore the timing of potential effects of the intervention on patient-centered and staff-centered outcomes, as well as how sustainable such effects are over different time periods. Additionally, assuming that ICU Support positively affects relevant patient and staff outcomes, asking for a termination of the intervention after a certain time period or withholding the intervention from the control group may be ethically questionable and may negatively influence the compliance of ICU staff to participate in the study.

## Methods: participants, interventions, and outcomes

### Study setting {9}

The study will be carried out at nine university hospitals, all of them located in Germany: University Hospital RWTH Aachen, University Hospital Augsburg, Charité – University Medicine Berlin, University Hospital Carl Gustav Carus Dresden, University of Leipzig Medical Center, University Medical Center Schleswig–Holstein Campus Lübeck, University Medical Center Mainz, University Hospital LMU Munich, University Hospital Würzburg. The participating ICUs at the 9 hospitals vary in size, with a range from 51 to 212 employees and an average of 118.4 (SD 49.4) employees.

### Eligibility criteria {10}

#### ICU patients

To be eligible for inclusion in this study, patients have to be admitted to a participating ICU with a minimum length of stay of at least 24 h. Participants are excluded if they are younger than 18 years old, pregnant, or are transferred between study sites during the study period.

#### ICU staff

ICU staff of participating units from study centers involved in patient care (medical service, nursing, therapeutic service including physiotherapists, speech therapists and psychologists, and auxiliary assistants) will be included in the study. Staff will be excluded from study participation if they are younger than 18 years old or if they are involved in activities at multiple study centers during the duration of the study.

### Who will take informed consent? {26a}

Patient-centered outcomes will be anonymously obtained at the unit level at each study site via digital patient records as part of the routine documentation of patient care. Since patients will not receive any study-related intervention directly, they will not be included as study participants but define the patient population through which the quality of care is assessed at each site. Staff-centered outcomes will also be anonymously obtained at the unit level via the Human Resources (HR) department of each clinic and via an online questionnaire using the software SoSci Survey. This software meets the national and international legal requirements for data protection (BDSG, DSG-VO and state laws, ISO-certified). Prior to the participation in the questionnaire, ICU staff will be informed about the study that their participation is voluntary and that non-participation will not result in any negative consequences. Moreover, they will be informed that they can withdraw their participation at any time without providing any reason. Participants can only access the questionnaire after providing online informed consent to participate in the online surveys.

### Additional consent provisions for collection and use of participant data and biological specimens {26b}

All study data will serve only scientific purposes and will be collected and stored anonymously. This study will not involve collecting biological specimens for storage.

## Interventions

### Explanation for the choice of comparators {6b}

The comparison between the number of intensive care complications per patient during the stay in the intensive care unit between study groups was chosen because intensive care complications reflect an important indicator for patient safety at ICUs. This composite measure therefore serves to evaluate the effectiveness of ICU Support on the quality of patient care. Additionally, the comparison between the amount of sick-related leave hours relative to the amount of planned working hours serves to evaluate the effectiveness of ICU Support on sick-related absence of ICU staff; an important indicator of employees’ occupational health and well-being and a factor causing significant payroll costs in hospitals.

### Intervention description {11a}

ICU Support is based on the Circle Up framework [9] and involves three types of main activities that occur on a daily level: (1) *Briefings*, which take place at the beginning of a shift with the whole team or prior to a specific procedure with the team members involved in the activity to plan team-based activities together, [2] *Informal peer check-ins* that take place on an as-needed basis during the shift to offer peer support, and (3) *Debriefings*, which take place at the end of the shift or after a specific procedure to collectively reflect on team successes, to identify critical incidents, to collectively learn from errors, and to establish team needs and learning points to improve work processes and team interaction in the future. Moderators/leaders of the daily briefings or debriefings will be leading personnel from the medical service and nursing that participated in the ICU Support training sessions (see below). Once ICU Support has been fully and regularly implemented, the role of the moderator may be taken up by any team member who feels comfortable in this role and is a trained debriefer. Importantly, the lead of the team meetings should switch between different professions (e.g., physicians, nurses) to ensure high interdisciplinary participation. Figure 2 depicts a visualization of the core elements of ICU Support.

**Fig. 2 Fig2:**
[figure not shown]
ICU Support. *Note.* Based on Rock et al. (2020) [9], Center for Medical Simulation, NEJM Catalyst (catalyst.nejm.org) © 2020 Massachusetts Medical Society

To ensure that ICU Support is successfully implemented at each site, leading professionals of participating ICUs (physicians, nurses) attended a thorough training program prior to the implementation. The training program involved three modules: The first module consisted of a 4-h module in which ICU Support, underlying central team principles (e.g., error management) and their value were introduced. Questions such as “*What is ICU Support? Why is it valuable to us? What makes team meetings successful?*” were collectively discussed and answered in an interactive, face-to-face format. The second module consisted of a 2-h online session in which relevant communication and debriefing techniques were taught to participants and practiced in the form of interactive role-plays. The third module also consisted of a 2-h online session which was specifically dedicated to work out the local implementation strategy of ICU Support at each site (e.g., “*When and where will we conduct the regular team meetings? Who will join? Which practical challenges do we anticipate and how can we solve these?*”).

In addition to the three training modules, the Principal Investigators (PIs) at each site were asked to name 1–2 local contact persons with debriefing experience who were not part of the ICU teams and could locally help operationalize and sustain the ICU Support intervention (e.g., safety-quality staff, psychologists). The local contacts attended the three training modules as described above and received an additional 2-h training on how to monitor and debrief the ICU Support meetings. Prior to the official start of the ICU Support intervention, ICU teams of the participating centers got acquainted with the intervention during a 2-week accommodation phase (a so-called *wash-in* phase). During this phase, ICU team members had the opportunity to try out how to best implement the ICU Support team meetings in their daily clinical practice and adjust their approach if needed (e.g., meeting time, meeting structure, meeting location). Particularly during these 2 weeks, local contacts closely monitored the ICU Support team meetings and provided regular feedback to the ICU teams to assist the effective implementation of the intervention.

All training modules were conducted by the same team of debriefing experts and clinicians who were familiar with the ICU Support concept and corresponding operationalization. The training modules were typically distributed over a period of 4 weeks and completed prior of the implementation of ICU Support. Figure 3 shows the implementation process of ICU Support.

**Fig. 3 Fig3:**
[figure not shown]
ICU Support implementation process

### Criteria for discontinuing or modifying allocated interventions {11b}

Allocated interventions will not be discontinued or modified throughout the trial period.

### Strategies to improve adherence to interventions {11c}

Adherence to the intervention will be monitored and documented by the moderators of the ICU Support team meetings by means of a checklist. The checklist will be filled in daily and includes a documentation about whether the Briefing and Debriefing took place on the respective day.

### Relevant concomitant care permitted or prohibited during the trial {11d}

There will be no restrictions on concomitant patient care during the trial.

### Provisions for post-trial care {30}

ICU Support is a structured meeting and support concept for ICU staff developed to promote interprofessional communication, peer support, and patient safety. The intensive care processes themselves are not influenced by the intervention. It is not expected that the implementation of ICU Support will have any negative impact on ICU staff or ICU patients and thus, no specific provisions for post-trial care are required.

### Outcomes {12}

#### Patient-centered primary outcome

Number of intensive care complications per patient during the stay in the intensive care unit during T1. The definition of complications is a priori based on the classification scheme according to Clavien and Dindo [13]. This includes a 5-level graduation of complications by severity. The primary outcome only considers the number of complications, not their severity. Data collection of patient-centered outcomes will be retrospectively obtained from patient records at each participating study center and will be coded by trained study staff.

#### Staff-centered primary outcome

Sick-related absence data for ICU staff will be obtained anonymously at the unit level via the HR department of the participating study center. To make this data comparable across study centers, we assessed sick-related absence as the amount of sick-related leave hours relative to the amount of planned working hours during T1.

#### Patient-centered secondary outcomes

The patient-centered secondary outcomes include the average severity of intensive care complications per patient during their ICU stay in period T1, the number of intensive care complications per patient during their ICU stay in period T2, the average severity of intensive care complications per patient during their ICU stay in period T2.

#### Patient-centered control variables

Control variables include age of patients, gender of patients, previous illnesses, and their total length of stay in the ICU.

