#### ICU patients

An analysis of covariance (ANCOVA; fixed effects, main effects, and interactions) with two groups, two measurement times (T0 and T1), and 4 covariates (age, sex, previous illnesses, and length of stay) was scheduled to calculate the appropriate sample size. Assuming a small effect of *f* = 0.10 according to Cohen (1988) [16], an alpha error level of 0.05 and a power of 90%, the total sample size was *N* = 1053. To account for an expected dropout of 10%, a total number of 1110 patients will be targeted.

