#### T1

Data collection period T1 will start 1 month after the start of the study and will last for 45 days. Equivalent to T0, patient-centered data will be collected during the first 45 days of T1, and sickness-related absence will be obtained during the first 30 days. Questionnaire data will be collected during the last 14 days of T1.

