## Statistical methods

### Statistical methods for primary and secondary outcomes {20a}

Data will be analyzed with IBM SPSS Statistics software version 25 (IBM Corp., Armonk, NY, USA). To analyze the effect of the ICU Support intervention on the patient-centered primary outcome, an analysis of covariance with time as the within-subject factor (T0 and T1), study group as the between-subject factor (intervention and control), and 4 covariates (age, sex, previous illnesses, and length of stay) will be conducted. Significance will be determined by two-sided 95% confidence intervals.

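### Total ICU length of stay, settled only after exposure and after the counted complications, is a covariate in the primary patient model and can pull the estimated effect toward zero

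*Protocol article*

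**What the plan says.** The section on patient-centered control variables reads "Control variables include age of patients, gender of patients, previous illnesses, and their total length of stay in the ICU". Section {20a} builds the primary patient model on time period and study group, and its covariate list includes length of stay: "4 covariates (age, sex, previous illnesses, and length of stay) will be conducted". The sample-size section {14}, under ICU patients, names the same four covariates.

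The outcome is "Number of intensive care complications per patient during the stay in the intensive care unit during T1". The hypothesis in {7} is that the intervention "reduces the occurrence of complications in intensive care patients".

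On timing, the description of arm 1 says "With the start of the study, the managers introduce the ICU Support elements into the daily work routine of their units", and the T1 section says "Data collection period T1 will start 1 month after the start of the study and will last for 45 days".

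Section {20a} judges significance by two-sided 95% confidence intervals, and {20b} plans no further analyses. The protocol gives no reason for the length-of-stay covariate. It does not limit it to the stay before a first complication, does not use it as an exposure offset, and plans no model without it.

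**The concern.** Age, sex and previous illnesses are fixed at admission, so the intervention cannot change them. Total length of stay is different. In the intervention arm, every T1 patient's stay unfolds after ICU Support has begun, and its final value is known only once the complications of that stay have happened. If a complication lengthens the stay, length of stay is partly a result of the outcome.

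A model that holds it constant compares patients who ended with equal stays. It then removes the part of the difference in complications that also shows up as a difference in stay. At stake is the main patient-centered number the trial will report: the reduction in complications per patient and its interval. No unadjusted or differently adjusted estimate is planned beside it.

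**Working it through.** **1. The plan's own figure.** Inputs from {14}: f = 0.10, alpha 0.05, power 90%, 4 covariates. Two groups and two times give 4 cells. Noncentral F with 1 numerator df: noncentrality f² × N = 0.01 × 1053 = 10.53, denominator df = 1053 − 4 − 4 = 1045, power 0.9001. N = 1053 is reproduced. With 3 covariates (length of stay dropped) and f still 0.10, N is again 1053.

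**2. Why the coefficient moves.** Let x be exposure, b the stay a patient would have without complications, and y the count, with y = τx + ρb + e. Let the total stay be L = b + d·y, where d is the days added per complication. Write s² for the variance of b and σ² for that of e. Then, given x:

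- Cov(y, L) = ρ(1 + dρ)s² + dσ²
- Var(L) = (1 + dρ)²s² + d²σ²
- exposure shifts L by dτ

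The adjusted coefficient is τ − dτ × Cov(y, L)/Var(L), so the share of τ kept is

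(1 + dρ)s² / [(1 + dρ)²s² + d²σ²].

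This equals 1 at d = 0. For d > 0 and ρ ≥ 0 it lies between 0 and 1, which is shrinkage toward zero. If τ = 0, the adjusted coefficient is also 0.

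**3. Illustrative size.** The documents give neither d nor the complication rate, so all of the following is assumed: rate ratio 0.8; 0.1 or 0.2 complications per ICU day; patient frailty; counts proportional to the underlying stay (mean about 5 days); independent patients without centre effects; 2,000,000 patients per scenario. The group-by-time coefficient (complications per patient) was estimated by least squares without and with total stay. Shares use unrounded coefficients.

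| Added days per complication | Rate 0.1: without / with / kept | Rate 0.2: without / with / kept |
|---|---|---|
| 0 | −0.120 / −0.119 / 98% | −0.243 / −0.241 / 99% |
| 0.5 | −0.117 / −0.105 / 90% | −0.232 / −0.197 / 85% |
| 1 | −0.123 / −0.098 / 80% | −0.253 / −0.162 / 64% |
| 2 | −0.117 / −0.076 / 65% | −0.234 / −0.113 / 48% |
| 3 | −0.119 / −0.061 / 52% | −0.238 / −0.086 / 36% |

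With no true effect, both coefficients stayed within 0.006 of zero. Another set-up (mean 1 complication per patient, true 20% reduction) kept 99%, 90%, 70%, 55% and 45% at 0, 1, 2, 3 and 4 added days. Further settings at rate ratio 0.8 kept 46% to 98% over 0.5 to 4 days and 100% at 0 days.

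**4. The test statistic.** Adjustment also lowers the residual SD. In the table's scenarios the standardized effect rose by a factor of 1.13 to 1.40. The ratio of the adjusted to the unadjusted t statistic at 0, 1, 2, 3 and 4 added days was:

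- counts proportional to time at risk: 1.32, 1.27, 1.22, 1.13, 1.08
- counts independent of time at risk: 1.01, 0.98, 0.92, 0.85, 0.77

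Further settings ranged from 0.72 to 1.13.

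**The case against.** The strongest defence is that length of stay is also time at risk. The outcome is a count over stays of any length from 24 hours, a longer stay offers more opportunity for complications, and no other listed covariate captures this. That stands as a plausible reason for including it. It does not rescue the model as written: a linear covariate on total stay does not separate exposure time from stay caused by complications, and a rate per ICU day is a different estimand from a count per patient and would have to be declared.

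Second, no passage says that complications prolong the stay. Fatal complications would shorten it, so both the size and, in part, the direction rest on a clinical assumption. This also stands.

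Third, a reader might infer that the test is invalid, that power is lost, or that the hypothesis in {7} is no longer addressed. The documents do not support this: with no true effect the adjusted estimate stayed at zero, and the test statistic rose in some settings and fell in others.

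Fourth, a reader might add that total stay cannot be time at risk because only events inside the 45-day window count. The outcome definition can equally mean all complications in the stays of T1 patients, and on that reading total stay is the time at risk.

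The full analysis plan is not shown, but this is not a matter left open for it: the protocol itself fixes the covariate in three places.

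**Conclusion.** The point holds for the effect estimate and its confidence interval. The only planned primary patient analysis adjusts for a variable settled after exposure and after the counted events. Provided that complications on balance prolong the ICU stay, the estimated reduction per patient is biased toward zero. Under a true 20% reduction and 0.5 to 4 added days per complication, roughly 36% to 98% of the effect is kept. These are scenario results, not estimates for this trial, and the bias essentially vanishes at 0 added days or with no effect.

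Nothing here shows that N = 1053 is wrong or that the trial loses power.

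**What to change.** Remove length of stay from the covariates of the primary patient model in {20a} and {14}, and adjust only for variables fixed at admission: age, sex and previous illnesses. Reword the control-variables section to match. Because length of stay is also time at risk, add complications per ICU day as a labelled supplementary rate analysis, and say that it answers a different question. Analyse length of stay as an outcome if it is of interest. Make the change before the outcome data are analysed.

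No data collection changes, but the change is not free. For two equal groups f = difference / (2 × residual SD). Dropping a covariate that predicts the count raises the residual SD, so the same raw difference corresponds to a smaller f. N stays at 1053 only while f = 0.10 is kept. If f fell to 0.09 (residual SD up by 1/0.9 = 1.11), the same formula gives N = 1300; at 0.08 (up by 1/0.8 = 1.25) it gives 1644. Where complications prolong the stay, the unadjusted difference is also larger, which works the other way. Section {14} should therefore say that f = 0.10 refers to the model without length of stay.
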